### Outcome measures

This study includes two co-primary outcome measures, reflecting structural status and functional status.

1. The proportion of people who show ‘disease progression’ in the eye with early AMD during the 12 months of the study based on an increase in drusen volume beyond test-retest repeatability limits or a progression to advanced AMD. Software available for the Cirrus optical coherence tomography (OCT) system allows automated assessment of drusen volume. Irrespective of initial drusen volume, approximately 50% of people with AMD show a significant increase in drusen volume over the 12-month study period, that is, beyond test-retest 95% confidence intervals [42]. Conversion to advanced disease will also be considered to be an indicator of disease progression in this analysis. Data from a trial on a similar group indicates that about 10% of people meeting our inclusion criteria will develop advanced AMD within 12 months [43]. Hence, 60% of participants might be expected to show progression based on increased drusen volume or progression to late AMD. The development of advanced AMD will be determined on the basis of ophthalmologist diagnosis at the monthly follow-up appointments at the nAMD clinic.

2. The rate of retinal adaptation (time taken for photoreceptors to recover their sensitivity after being exposed to a bright adapting light).

Secondary outcome measures include: the change in drusen volume over the 12 month follow-up period; the number of ranibizumab retreatments required during the year in the fellow eye with nAMD (assessed through review of medical records at the end of 12 months); changes in visual function including chromatic thresholds, visual acuity and psychophysical 14 Hz flicker thresholds; self-report outcome measures, including health-related quality of life (EQ-5D) and visual function (VFQ-48) [44]; a sleep quality questionnaire (PSQI) and a semistructured interview (conducted monthly by interview) to determine intervention acceptability.

To obtain detailed information about the time course of any therapeutic action, the primary and the first of the secondary outcome measures (based on drusen volume) will be assessed at baseline and then at monthly intervals (using OCT images obtained at the regular nAMD clinic follow-up appointments).

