### Randomization

Participants will be stratified according to risk of AMD progression (using the AREDS simplified scale [45]), and randomly allocated to receive either the light mask or no intervention in a 1:1 ratio using computer-generated random permuted blocks (both groups will continue to receive ranibizumab injections as required for the fellow eye). The study investigator will be provided with three piles of envelopes by the chief investigator, in order to randomize the participant to either the intervention or control arm of the study. Each pile relates to a different stratum of randomization, that is, grade 2, 3 or 4 of AMD, according to the AREDS simplified scale. The envelopes in each pile will be numbered, and will contain the randomization allocation for each participant.

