### Statistical methods

It should be noted that, as a Phase I/IIa proof-of-concept study, this research is designed to assess the acceptability of this therapy for the participants, and to provide preliminary data to support a larger Phase III randomized controlled trial in the future, and so is not powered to detect small effect sizes. To maximize retention, all follow-up visits will be timed to coincide with scheduled appointments at the nAMD clinic. We will aim to recruit 60 people, which, allowing for 15% dropout through the year, should leave a final cohort of 51. This will be sufficient to detect a 50% reduction in people showing progression at a probability level of 0.2, with a power of 80%, and a change in the time constant of cone adaptation of 1 minute to be detected at a probability level of 0.05, with a power of 80%. The additional 40 participants enrolled into the cross-sectional part of the study will allow a total cohort of *n* = 100 to address secondary aim 4.

Analysis will be carried out on an intention-to-treat basis. There will be no interim analysis, but conversions to nAMD in the eye with early AMD at baseline, and ranibizumab retreatments for the fellow eye, will be recorded at each participant visit to the nAMD clinic for safety monitoring purposes.

This trial will primarily be concerned with providing information about the safety of the device in the treatment of AMD, and the magnitude of any treatment effect. On this basis, descriptive statistics will be carried out to summarize the demographic characteristics of the two groups, as well as the proportion of individuals showing disease progression in each group, the magnitude of changes in secondary outcome measures, including drusen volume, measures of visual function, and the self-report tests, and the fellow eye retreatment rates.

The primary outcome measure will be the proportion of patients demonstrating disease progression at 12 months. Comparisons will be performed using stratified Mantel-Haenszel tests and presented as forest plots.

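### The expected 60% progression rate assumes that nobody meets both components, which makes the 80% power optimistic if the 0.2 level is two-sided

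*Protocol article*

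**What the plan says.** Under Outcome measures, the first co-primary outcome is the proportion of participants who progress in the early-AMD eye, "based on an increase in drusen volume beyond test-retest repeatability limits or a progression to advanced AMD". Either event is enough.

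The same paragraph gives a rate for each component, from two separately cited sources:

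- Drusen: "approximately 50% of people with AMD show a significant increase in drusen volume over the 12-month study period".
- Conversion: "about 10% of people meeting our inclusion criteria will develop advanced AMD within 12 months".

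It then concludes: "Hence, 60% of participants might be expected to show progression based on increased drusen volume or progression to late AMD". Overlap between the two is not discussed.

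Under Statistical methods, the sample size is set out as follows: "We will aim to recruit 60 people, which, allowing for 15% dropout through the year, should leave a final cohort of 51". The power claim is: "This will be sufficient to detect a 50% reduction in people showing progression at a probability level of 0.2, with a power of 80" per cent. That sentence gives no control rate and does not say whether the level is one- or two-sided. The planned comparison is described so: "Comparisons will be performed using stratified Mantel-Haenszel tests and presented as forest plots". Under Randomization, participants are "randomly allocated to receive either the light mask or no intervention in a 1:1 ratio using computer-generated random permuted blocks".

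**The concern.** The probability of an either/or outcome equals the sum of its two parts only when they never occur in the same person. Here that means no participant who converts to advanced AMD also has a qualifying drusen increase. The protocol gives no reason to expect this. Its Statistical methods section treats drusen volume as a validated marker of progression, which points towards overlap.

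The sum is therefore the top of the range that the quoted figures allow, but the protocol uses it as the expectation. With a fixed relative reduction, a lower control rate gives a smaller absolute difference and less power. The power statement for this outcome could then be too favourable, and the same added rate could be carried into the sample size of the later Phase III trial that these data are meant to support.

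**Working it through.** **Inputs.** Drusen increase 50%, conversion 10% and composite 60% (Outcome measures). 60 recruited, 15% dropout, 50% reduction, level 0.2, power 80% (Statistical methods). 1:1 allocation (Randomization). Assumption: the 60% is the control rate behind the power sentence. The protocol does not say so, but the figure reproduces with it.

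**Evaluable number.** 60 × 0.85 = 51, or 25.5 per arm. This agrees with the protocol.

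**Composite rate.** P(A or B) = P(A) + P(B) − P(both).

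- No overlap: 0.50 + 0.10 − 0 = 0.60.
- Independence: 0.50 + 0.10 − 0.05 = 0.55.
- Every converter also has a drusen increase: 0.50 + 0.10 − 0.10 = 0.50.

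There is a second route to 55%. If the 50% drusen rate applies to the 90% who do not convert, the composite is 0.90 × 0.50 + 0.10 = 0.55. To reach 60% by this route, the drusen rate among non-converters would have to be 0.50 / 0.90, or about 56%.

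**Power formula.** This is the two-proportion normal approximation with pooled variance under the null, n = 25.5 per arm, p₂ = p₁/2 and p̄ the mean of the two:

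z = [ (p₁ − p₂) − z_crit × √(2p̄(1 − p̄)/n) ] / √( [p₁(1 − p₁) + p₂(1 − p₂)]/n ), and power = Φ(z).

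**The protocol's figure first.** For 60% versus 30%, two-sided 0.2 (z_crit = 1.2816):

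- √(2 × 0.45 × 0.55 / 25.5) = 0.1393, and 1.2816 × 0.1393 = 0.1786.
- √((0.24 + 0.21) / 25.5) = 0.1328.
- z = (0.30 − 0.1786) / 0.1328 = 0.914, so power = 82.0%.

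This reproduces the stated 80%. A one-sided level of 0.1 gives the same value. A simulated Mantel-Haenszel test with three equal strata gives 80.8%, so the stratified form of the test does not alter the result.

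**The same calculation over the range**, with z_crit = 0.8416 for one-sided 0.2:

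| Control vs treated | z, two-sided 0.2 | Power, two-sided 0.2 | Power, one-sided 0.2 |
|---|---|---|---|
| 60% vs 30% | 0.914 | 82.0% | 91.6% |
| 55% vs 27.5% | 0.743 | 77.1% | 88.5% |
| 50% vs 25% | 0.582 | 72.0% | 85.0% |

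**Break-even.** With 51 evaluable, power is 80% at a control rate of about 58% if the level is two-sided, and about 44% if one-sided.

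**Recruitment for 80% power, two-sided 0.2.** 24, 28 and 33 per arm at 60%, 55% and 50%. After 15% dropout: 48/0.85 → 57, 56/0.85 → 66 and 66/0.85 → 78, against 60 planned.

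**The case against.** The strongest reply is that the stated power is correct on the protocol's own inputs. That stands: 60%, a halving, 51 evaluable and two-sided 0.2 give 82%. A reader might infer that the power calculation itself is wrong. It is not; the weak link is the control rate fed into it.

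Next, the two-sided reading is an inference. It also stands that on a one-sided reading the claim is met at every rate from 50% to 60%. Two-sided 0.2 is the better fit to a stated 80%, since one-sided 0.2 at 60% would give about 92%, but fit does not prove intent.

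Third, the inputs are rough and hedged. A drusen rate of 55% with 10% conversion gives 0.55 + 0.10 − 0.055 = 59.5% under independence, and power of 81.5%. Safety monitoring cites a one-year nAMD incidence of 12.2% (interval 1.7% to 30.6%); with 50% for drusen, independence gives 0.50 + 0.122 − 0.061 = 56.1% and power of about 78%. A 3-point shortfall at 55% is small beside this uncertainty. That limits the size of the point but does not justify addition without overlap. The 50% end is also only a bound, as nothing in the protocol says that nearly all converters show drusen growth.

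The caveat that the study is not powered for small effects does not answer the point, because the effect at issue is the declared halving.

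Two stronger readings are not supported. One is that the trial has little better than even odds of success at the 0.05 level: the protocol openly declares 0.2 for this outcome and keeps 0.05 for cone adaptation. The other is that the Mantel-Haenszel test would lose power through a continuity correction: the protocol mentions none, and that choice can be left to an analysis plan.

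**Conclusion.** The point holds in a limited form. The 60% is the no-overlap maximum of the two quoted rates; those figures support a range of 50–60%, with 55% under independence. If the 0.2 level is two-sided, which is the reading that reproduces the stated power, power for a halving is about 77% at 55% and 72% at 50%. That is roughly 3 and 8 points below the stated 80%, which is reached only at a control rate of about 58% or more. If the level is one-sided, power is 85–92% and there is no shortfall.

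This rests on three assumptions: that the 60% is the control rate behind the power sentence, that the quoted rates are taken at face value, and that the arms are equal with 51 evaluable in total. Neither the declared 0.2 level nor the arithmetic of the power calculation is at fault.

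**What to change.** In Outcome measures, replace the expected 60% with a range of 50–60%, noting that 55% follows if the two components are independent and 60% only if they never coincide.

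In Statistical methods, name the control rate used, say whether the 0.2 level is one- or two-sided, and give the power for a 50% reduction with 51 evaluable participants as about 72–82% if two-sided, or 85–92% if one-sided.

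The cost is a few sentences and, on the two-sided reading, a slightly less favourable power statement. For a proof-of-concept trial, no change in sample size is needed.

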### Participant timeline

The study flow diagram (Figure 1) outlines the appointment schedule. In brief, potential participants are identified at their first visit to the nAMD clinic. At the second visit (1 month later), informed consent will be obtained, and screening tests and baseline questionnaires will be carried out. At the third monthly visit, baseline functional tests will be carried out, and participants will be randomly assigned to either the treatment or intervention group. Participants in both intervention groups will attend a short, monthly follow-up appointment following their routine appointment at the nAMD clinic throughout the year. Final outcome data will be collected from control and intervention groups at a 12-month follow-up appointment, scheduled to follow a regular visit to the nAMD clinic.

**Figure 1 F1:**
[figure not shown]
Study flow diagram showing participant timeline.

Participants in the cross-sectional baseline study will attend Cardiff University or the Bristol Eye Hospital for one visit only.

### Recruitment

Sixty participants will be recruited to the trial. Ophthalmologists will identify potential trial participants who are attending for their first appointment at the nAMD clinic at Bristol Eye Hospital, and will provide them with an information sheet and ask for their permission to be contacted by the study investigators. The potential participants will be contacted at least 2 days after their receipt of the information sheet, and invited to meet the study investigator at their next visit to the nAMD clinic (approximately 1 month later) to discuss the trial, provide consent if they choose to participate, and carry out some basic screening tests. Participants will be informed after this screening visit whether they are eligible to take part in the study. Owing to the low number of patients required to participate in the study it is planned for the trial and data collection to take place principally at a single NHS centre, that is, the Bristol Eye Hospital. If needed, additional participants will be recruited from supplementary recruitment centres to ensure that targets are met.

Forty control participants and participants with grade 1 AMD (AREDS simplified scale [45]) for the baseline cross-sectional analysis will be recruited by local optometrists in Bristol and Cardiff, from a database of elderly volunteers, from the Bristol Eye Hospital, from the list of research volunteers at the Cardiff University Eye Clinic and from staff and students of Cardiff University.

### Randomization

Participants will be stratified according to risk of AMD progression (using the AREDS simplified scale [45]), and randomly allocated to receive either the light mask or no intervention in a 1:1 ratio using computer-generated random permuted blocks (both groups will continue to receive ranibizumab injections as required for the fellow eye). The study investigator will be provided with three piles of envelopes by the chief investigator, in order to randomize the participant to either the intervention or control arm of the study. Each pile relates to a different stratum of randomization, that is, grade 2, 3 or 4 of AMD, according to the AREDS simplified scale. The envelopes in each pile will be numbered, and will contain the randomization allocation for each participant.

### Masking

It is not appropriate in this study to use a sham treatment, since a non-illuminated mask may have a physiological effect on the retina and patients would be aware that they weren’t perceiving light and so would be unmasked to their intervention group. The study investigator who collects the outcome data will also be providing the masks and instructions on its usage and, hence, will not be masked to the intervention group. However, the potential for experimenter bias is limited, as the primary outcome measure, disease progression, is an objective measurement carried out by automated computer software. The ophthalmologists who are seeing the participants for their regular ranibizumab injections will be masked, which will prevent any bias in their retreatment decisions for the fellow eye.

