**Methods/design:**

ALight is a Phase I/IIa, multicentre, randomized controlled trial. Sixty participants (55 to 88 years old) with early AMD in one eye and neovascular AMD (nAMD) in the fellow eye will be recruited from nAMD clinics. They will be randomized (in the ratio 1:1), either to receive the intervention or to be in the untreated control group, stratified according to risk of disease progression. An additional 40 participants with healthy retinal appearance, or early AMD only, will be recruited for a baseline cross-sectional analysis. The intervention is an eye mask that emits a dim green light to illuminate the retina through closed eyelids at night. This is designed to reduce the metabolic activity of the retina, thereby reducing the potential risk of hypoxia. Participants will wear the mask every night for 12 months. Ophthalmologists carrying out monthly assessments will be masked to the treatment group, but participants will be aware of their treatment group. The primary outcome measure is the proportion of people who show disease progression during the trial period in the eye with early AMD. A co-primary outcome measure is the rate of retinal adaptation. As this is a trial of a CE-marked device for an off-label indication, a further main aim of this trial is to assess safety of the mask in the cohort of participants with AMD.

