The ETDRS visual acuity will be assessed in each eye. Chromatic thresholds will be measured for the eye with early AMD using the Colour Assessment and Diagnosis test [48] (City Occupational Ltd). Contrast thresholds to a 14 Hz flickering stimulus will be measured for the eye with early AMD using the procedure outlined by Dimitrov et al. [49]. The rate of parafoveal cone dark adaptation will be determined for the eye with early AMD using a psychophysical procedure described previously [50]. Thresholds will be determined using a psychophysical method, based on a ‘3 down, 1 up’ staircase paradigm [50]. An array of white light-emitting diodes behind a diffusing filter will be used to light-adapt photoreceptors in the central 43.6° of the test eye (the output of the white light-emitting diodes will be modified by a Lee filter, HT015, to provide a retinal illuminance of 5.20 log phot Td.s^-1^, providing a bleach of 85% cone photopigment and 74% rhodopsin). All light levels fall within the safety guidelines set out in British Standard BS EN 15004-2 (2007) [51]. There will be an initial training phase, of around 5 minutes, then the adapting light will be presented, and finally recovery of visual thresholds will be monitored for 25 minutes after exposure to the adapting light.

Those individuals who are assigned to the treatment group will then be given a light mask, and provided with written and oral instructions on its use. There will also be a reprise of the key information provided in the participant information letter about follow-up appointments. Participants will be given written copies to take home of the PSQI questionnaire that will be used in the monthly interview.

#### **
*Monthly assessment*
**

The investigator will access the OCT images and medical records of all participants after they have attended the ranibizumab clinic for each monthly follow-up appointment. This will allow measurement of drusen volume on a monthly basis, which will allow the final analysis to include an assessment of the time course of any therapeutic action. Additionally, reviewing medical records will facilitate monitoring of the conversion rate to advanced AMD in the control and intervention groups in the eye with early AMD at baseline, and of ranibizumab retreatment rates in the eye with nAMD, for adverse event reporting purposes.

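### Retinal adaptation is declared co-primary but dropped from the masking argument and the named primary analysis, so the claim of limited bias does not cover it

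*Protocol article*

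**What the plan says.** **Status of adaptation.** The Abstract states: "A co-primary outcome measure is the rate of retinal adaptation". The Outcome measures section agrees: "This study includes two co-primary outcome measures, reflecting structural status and functional status". The sample-size paragraph in Statistical methods sizes the trial for progression at level 0.2 and also for "a change in the time constant of cone adaptation of 1 minute to be detected at a probability level of 0.05", each with 80% power.

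**One primary elsewhere.** Later in Statistical methods the text reads "The primary outcome measure will be the proportion of patients demonstrating disease progression at 12 months", followed by stratified Mantel-Haenszel tests. No test is named there for adaptation. The ANCOVA sentence covers secondary outcomes and gives functional tests as an example, without naming adaptation. The sentence on the seventh secondary aim identifies the primary outcome as drusen volume, although Outcome measures lists change in drusen volume as secondary.

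**Masking.** The investigator who collects outcome data "will not be masked to the intervention group". The section nevertheless holds that "the potential for experimenter bias is limited, as the primary outcome measure, disease progression, is an objective measurement carried out by automated computer software". The Abstract adds that "participants will be aware of their treatment group". For the adaptation test, Data collection methods says: "Thresholds will be determined using a psychophysical method". This is a staircase procedure, with recovery followed for 25 minutes after the adapting light.

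**The concern.** The labels cannot all be true. Progression is one of two primaries in some places and the only primary in others, and drusen volume is the primary in a third. If the co-primary label stands, the masking rationale leaves out half of the primary assessment. The half left out is the one that depends on responses from a participant who knows the allocation, tested by an investigator who also knows it.

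At stake is how a result on adaptation should be read. A nominal p below 0.05 on an unmasked psychophysical measure could carry the weight of a primary finding, under a bias statement that was written for a different outcome. The two outcomes are also sized at different levels, and the article does not say how they are to be read together.

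**Working it through.** **1. The plan's own figure.** Inputs: 60 recruited and 15% dropout (Statistical methods); control progression 60% (Outcome measures), so 30% after a 50% reduction; 1:1 allocation (Randomization); level 0.2. Sidedness is not stated; two-sided is assumed here.
- Evaluable: 60 × 0.85 = 51, or 25.5 per arm.
- Power = Φ{(d√n − z·√[2p(1−p)]) / √[p₁(1−p₁) + p₂(1−p₂)]}, with d = 0.30, n = 25.5, p = 0.45 and z = 1.2816.
- This gives Φ{(1.515 − 0.902)/0.671} = Φ(0.914) = 0.82.

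The stated 80% for progression is reproduced. Fisher's exact test with 26 and 25 per arm gives 0.78.

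**2. Adaptation.** The article gives a 1-minute difference, level 0.05 and 80% power, but no standard deviation. With 25.5 per arm and a two-sided test, the implied SD is 1 / [√(2/25.5) × (1.960 + 0.842)] = 1.27 minutes (1.44 if one-sided). This is back-calculated, so it does not check the stated power.

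**3. What the missing status means for error rates.**
- Progression alone is primary: false-positive rate 0.20.
- Either outcome may count: 1 − (0.80 × 0.95) = 0.24 if independent. The upper bound for any dependence is 0.20 + 0.05 = 0.25. The increase over progression alone is 4 points, at most 5.
- Both are required: joint power is 0.80 × 0.80 = 0.64 if independent, or 0.82 × 0.80 = 0.66 with the recomputed figure. Positive correlation raises it, to at most 0.80. The worst-case false-positive rate is 0.20, which arises when only progression is null.

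**4. Does the masking argument cover each outcome?**
- Drusen-volume increase: measured by automated software. The argument applies.
- Conversion to advanced AMD: an ophthalmologist's diagnosis, so not automated. The Abstract and Masking section say these ophthalmologists are masked, so a different safeguard applies.
- Adaptation: not automated in the relevant sense, because thresholds come from the participant's responses. The investigator and the participant are both unmasked, so neither safeguard applies.

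Participant timeline and Data collection methods suggest that the baseline adaptation test comes before randomization and before the mask is issued, whereas the 12-month test follows a year of known allocation. Expectation could therefore enter the follow-up value only, and so the comparison between arms. Nothing in the document allows its size to be estimated.

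**The case against.** The strongest reply is that this is a condensed article for a proof-of-concept trial that describes itself as mainly concerned with safety and the magnitude of any effect. A decision rule and the adaptation analysis may sit in an analysis plan that is not shown. That stands, and the absence of a success rule would not be a finding alone. It does not settle the conflicting labels or the masking statement, which are in the text itself.

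A reader might go further in four ways that the documents do not support.
- *That success can be picked after the fact.* No section plans to declare the trial positive on either outcome, so this is conjecture.
- *That 24% is the harm.* Level 0.2 was chosen openly for progression, so only 4 to 5 points come from the unsettled status. Likewise, 64% rests on independence, and two measures of the same eye may well be positively correlated.
- *That adaptation is analysed in the secondary ANCOVA.* It is named neither there nor in the list of secondary visual-function measures. The text supports only that no analysis is named for it.
- *That conversion is assessed with bias.* The diagnosing ophthalmologists are stated to be masked.

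The staircase is rule-driven, which restricts the investigator's influence, and the lack of a sham is explained in the Masking section. Both points are fair. They narrow the exposure mainly to participant expectation and do not make the outcome automated.

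**Conclusion.** The point holds as an internal contradiction with a practical consequence. Adaptation is co-primary in the Abstract and Outcome measures and is separately powered at 0.05. It is missing from the primary named in Masking and Statistical methods, and drusen volume is given the primary label in one further sentence. The claim of limited experimenter bias is sound for automated drusen volume, incomplete for conversion (clinical but masked), and does not apply to adaptation.

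The numerical cost depends on which status is intended: about 24% against 20% for false positives if either result suffices, or about 64% joint power if both are needed. These figures take the stated levels and 80% powers at face value and assume independence. The stated power for progression is not in error and the sample size need not change. The bias in adaptation cannot be quantified from the document. This should be corrected, but it does not undermine the trial.

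**What to change.** Give adaptation one status in the Abstract, Outcome measures, Masking and Statistical methods. Two routes are acceptable:
- Progression as sole primary (level 0.2, stratified Mantel-Haenszel), with adaptation as key secondary (level 0.05, ANCOVA adjusting for its own baseline).
- Both kept as co-primary, with a named adaptation analysis and a stated rule for interpreting the two levels together, giving the resulting false-positive rate or joint power.

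On either route:
- Correct the sentence on the seventh secondary aim that labels drusen volume as the primary outcome.
- In Masking, limit the bias claim to the automated drusen-volume component, note that conversion is diagnosed by masked ophthalmologists, and state that adaptation and the other psychophysical and self-report outcomes are unmasked and open to expectation bias.
- Fit all adaptation curves with one fixed routine, on files with allocation and visit removed, and with rejection criteria set beforehand. This limits analyst discretion but does not remove participant expectation, so the Masking correction is still needed.

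The cost is wording and a coded export of the threshold data. Under the first route, adaptation also loses its co-primary label.
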